## **6. INVESTIGATIONAL PLAN**

### **6.1 VISIT SCHEDULE**

This study consists of two phases:

- 1) A pre-treatment characterization phase and
  - 2) A randomization / treatment phase.
1. During the pre-treatment characterization phase (Visits 1-3) both eligible patients with COPD and Age / Gender Matched Controls (see Section 3.3.1 Inclusion criteria), a training constant work rate test (Visit 2) and baseline constant work rate test (Visit 3). The pre-treatment characterization phase may be extended up to four weeks for administrative reasons.
  2. During the randomization and treatment phase, eligible COPD patients will be randomized into the first of two treatment periods of the study (Visit 3). Each treatment period will last six weeks with a four-week wash-out between each treatments. The follow-up visit (Visit 7) will take place 30 days after the end of last treatment period (Visit 6). A patient visit may be rescheduled twice due to lack of medication washout and/ or other restriction on test day compliance as long as it is within the acceptable time windows of the protocol. Any rescheduling of patients should be discussed with the Local Clinical Monitor.

### **6.2 TRIAL PROCEDURES AT EACH VISIT**

#### **6.2.1 Screening and run-in phase**

##### **Informed Consent (Visit 0)**

- Informed consent will be obtained prior to patient participation in the trial, which includes any medication washout procedures or restrictions (e.g., for exercise testing). Upon obtaining consent, the patient will be instructed on the medication washout and other restrictions for the screening pulmonary function testing and incremental work rate testing (Visit 1). See Section 5.1.2 for pulmonary function test restrictions and Appendix 10.3 for exercise test restrictions.
- Demographic data (gender, race, date of birth, height, weight, pack-years, and smoking status) will be recorded.
- Relevant medical history will be recorded.

## Initial Screening Visit (Visit 1)

### Observations and Procedures:

- Medication wash-out compliance will be verified and the 24-hour clock time of the last cigarette smoked during the 12 hours prior to the start of pulmonary function testing will be recorded.
- Physical activity questionnaires (VSAQ, WPAI-GH and the FACIT-short form) will be completed by the subject.
- Baseline Dyspnea Index (BDI) questionnaire will be completed by the subject.
- COPD background characteristics and duration will be recorded (if applicable).
- Physical examination including vital signs (blood pressure and pulse rate) and 12-lead ECG will be conducted. The vital signs (seated) and ECG should be conducted following five minutes rest and prior to the albuterol dosing.
- Urinalysis for pregnancy testing will be conducted (if applicable).
- For the COPD patients all adverse events experienced since signed informed consent will be reviewed and recorded. For the Age / Gender Matched Controls only SAEs will be reviewed and collected.
- Concomitant therapy for the previous three months will be recorded in the eCRF as described in Section 4.2.
- Body plethysmography measurements will be conducted in the morning between 7:00 -10:00 a.m. After the baseline tests, reversibility testing will be performed (see Section 5.1). Spirometry testing will be obtained within 5 minutes before, or up to 5 minutes after the scheduled time point.
- Patients will perform an incremental test (as described in [Appendix 10.3](#)) 90 minutes after pulmonary function reversibility tests are complete (the incremental exercise test must not be <45 minutes after or >150 minutes after pulmonary function reversibility tests are complete). The test duration and the maximum work rate of each patient will be recorded in the eCRF.

[figure not shown]

Figure 6.2.1: 1 Visit 1 timeline

- The baseline for rescue medication use will be established during the run-in period from Visit 1 to Visit 3. COPD patients qualified to enter the baseline portion of the study will be issued a patient specific diary, will receive instructions on completing the diary, and restrictions for the baseline period and subsequent visits reviewed. COPD patients qualified to enter the baseline portion of the study will also be issued albuterol HFA MDI and directions on the use of the MDI (for rescue medication use). Patients will be instructed to bring all issued medication (if applicable) and the diary to the clinic on the next scheduled visit. Additional albuterol MDIs will be issued at subsequent visits as needed.
- Both Age / Gender Matched Controls and COPD patients qualified to enter the baseline portion of the study will be given accelerometers and will be instructed how to use them.

### **Run –in period**

Age / Gender Controls and COPD patients who qualify at Visit 0 will enter the run-in period of the trial. Each site will be asked to provide control subjects of the same gender and  $\pm 5$  years of age of COPD patient randomized to receive study medication. (COPD patients and control subjects do not necessarily need to be from the same site.).

COPD patients who qualify at Visit 1 will measure and record in their diary, the number of puffs of albuterol medication used during the baseline period (Visit 1 to Visit 3).

COPD patients must satisfy **all** inclusion and exclusion criteria prior to randomization at Visit 3 (see Sections 3.2 and 3.3). In addition, if during this baseline period there is any indication that the patient is not stable enough to complete the study or that the patient will be non-compliant with the study medication or restrictions, then these patients should not be randomized.

If the baseline period is extended more than an additional 4 weeks, but not more than an additional 8 weeks, the baseline physical examination will be repeated. The repeat baseline examination will include vital signs (blood pressure and pulse rate), 12-lead ECG and pregnancy test. The patient should return for these evaluations two weeks prior to the rescheduled Visit 3. COPD patients should record the number of occasions of albuterol use during the 2 weeks preceding Visit 3 in their diary. All adverse events and concomitant therapies will be recorded. If the baseline period is extended more than an additional eight weeks, the Clinical Monitor should be contacted.

Details of any patient who is screened for the study but is found to be ineligible must be entered in an Enrollment Log and documented in the electronic Case Report Form.

### **Training Constant Work Rate Visit (Visit 2)**

Observations and Procedures:

- Medication washout compliance will be verified and the 24-hour clock time of the last cigarette smoked during the 12 hours prior to the start of the study visit will be recorded.
- Patients smoking status will be recorded.

- Collect patient diary to review rescue medication use since last visit.
- Accelerometer will be removed prior to testing procedures and re-dispensed after completing all visit procedures.
- For the COPD patients all adverse events experienced since the last visit will be reviewed and recorded. For the Age / Gender Matched Controls only SAEs will be reviewed and collected.
- Vital signs (blood pressure and pulse rate).
- Concomitant therapy for the previous three months will be recorded in the eCRF as described in [Section 4.2](#).
- Subjects will conduct the baseline constant work rate test at 80%  $W_{cap}$ . (80% of peak work rate in the incremental test).
- COPD patients will be instructed to return completed patient diaries and all rescue medication to the clinic on the next scheduled visit.

### 6.2.2 Treatment phases

#### First visit of each treatment period (Visits 3 and 5)

Patients will be contacted prior to each of the visits to remind the patient of medication wash-out times.

**Note: Age / Gender Matched Controls will participate through Visit 3 only; Age / Gender Matched controls will not be randomized to double-blind treatment.**

Observations / Procedures:

- Medication washout compliance will be verified and the 24-hour clock time of the last cigarette smoked during the 12 hours prior to the start of pulmonary function testing will be recorded at each visit.
- Patients smoking status will be recorded.
- Collect patient diaries to review rescue medication use since last visit.
- Accelerometers will be collected if applicable at Visit 3 only.
- Any adverse events and changes in concomitant therapies will be recorded at each visit.
- **Note: For Age / Gender Matched Controls only SAEs will be recorded.**
- Vital signs (blood pressure and pulse rate) will be measured. They will always be measured immediately before PFTs and with the patient seated and rested for at least five minutes.
- Pre-study drug spirometry (FEV1 and FVC) will be performed between 7:00 and 10:00 a.m. Spirometry testing will be obtained within 5 minutes before, or up to 5 minutes after the scheduled time point. Note: All subsequent visit PFTs (Visits 4 to 6) must be conducted within 30 minutes of the spirometry at Visit 3.
- Patients will also conduct a baseline constant work rate endurance test 60 minutes after pulmonary function tests are complete (the constant work rate endurance test must not be <45 minutes after or >150 minutes after pulmonary function tests are complete). The CWR test will be conducted at 80% of the maximum work rate (80%  $W_{cap}$ ) obtained during the incremental exercise test as described in [Appendix 10.3](#).

- At Visit 3, ONLY COPD patients will be randomized into the cross-over treatment phase of the study after all the inclusion and exclusion criteria have been met.
- Randomized patients will receive instructions on use of the HandiHaler® and the MDI, and restrictions for the treatment period and subsequent visits. The HandiHaler® training device can be used to train patients. Patients will be instructed to bring all study-related treatments to the clinic at each visit.
- Test medications will be dispensed to the randomized patient (see Section 4.1.3) for use the morning of the visit.

[figure not shown]

Figure 6.2.2: 1 Visit 3 and 5 timeline

- Randomized patients will be dispensed rescue medication as needed.
- Patients will be issued a paper diary to record trial medication administration and rescue medication use on a daily basis. Patients will be instructed to return to the clinic with the diary at the next scheduled visit so that the diary can be reviewed for treatment compliance.

If the patient is unable to complete the entire test-day visit, the electronic Case Report Form will be completed indicating the reason for stopping testing, rescue medication given and time of rescue medication. Patients who are unable to complete the test-day visit may leave the clinic only upon instruction from the supervising physician. The exact date and clock time of the last drug administration must be recorded in the eCRF (Termination of Trial Medication).

### Clinic visits after 6 weeks of each treatment period (Visits 4 and 6)

#### Observations / Procedures:

Patients will be contacted prior to each of the visits to remind the patient of medication wash-out times, exercise test restrictions and to bring back all study medication at their next visit.

- Medication washout compliance will be verified and the 24-hour clock time of the last cigarette smoked during the 12 hours prior to the start of pulmonary function testing will be recorded at each visit
- Smoking status will be recorded
- Collect patient diary to review rescue medication use and treatment compliance since last visit
- Collect all study medication dispensed at the last visit
- Any adverse events and changes in concomitant therapies will be recorded at each visit
- At Visit 6 only a physical exam will be completed. At both Visits 4 & 6 vital signs (blood pressure and pulse rate) will be measured immediately before spirometry and with the patient seated and rested for at least five minutes
- Spirometry (FEV1 and FVC) will be performed at the following times relative to the morning dose of study medication:

**Pre-dose:** 15 minutes prior to the dose of study medication

#### **Inhalation of study medication dose**

**Post-dose:** 1 hour 20 minutes after study medication dose

- measurements scheduled at 15 minutes prior to the dose will be obtained within  $\pm 5$  minutes of the specified time-points, and 1 hour 20 minutes post-dose will be obtained within  $\pm 15$  minutes of the specified time-points
- Patients will conduct a constant work rate endurance test at 2 hours 15 minutes  $\pm 15$  minutes post dose of trial medication. The CWR test will be conducted at 80% of the maximum work load (80% Wcap) obtained during the incremental exercise test as described in [Appendix 10.3](#).

[figure not shown]

Figure 6.2.2: 2 Visit 4 and 6 timeline

- At Visit 4, but not at Visit 6, patients will be issued a paper diary to record trial medication administration and rescue medication use on a daily basis. Patients will be instructed to return to the clinic with the diary at the next scheduled visit so that the diary can be reviewed for treatment compliance.
- No trial medication will be dispensed at this visit.
- At Visit 4 dispense rescue medication as needed for wash-out periods.

If the patient is unable to complete the entire test-day visit, the electronic Case Report Form will be completed indicating the reason for stopping testing, rescue medication given and time of rescue medication. Patients, who are unable to complete the test-day visit, may leave the clinic only upon instruction from the supervising physician. The exact date and clock time of the last drug administration must be recorded in the eCRF (Termination of Trial Medication).

### 6.2.3 End of trial and follow-up (Visit 7)

Following the end of the 2 x six-week cross-over period, patients will be followed up for an additional 30 days. They will be phoned at the end of this period (Visit 7) and their smoking status, adverse events and concomitant therapies will be recorded.

The clinical monitor must be consulted on all persistently abnormal tests and SAEs until it is agreed that follow-up is no longer necessary.

### 6.2.4 End of trial (premature withdrawal)

The investigator should make every effort to perform a follow-up phone call and collect all used and unused study medication from any patient who withdraws prematurely.

The local clinical monitor must be consulted on all SAEs until it is agreed that follow-up is no longer necessary. Additionally, all SAEs that occur within 30 days after a patient terminates study medication must be reported according to Boehringer Ingelheim SAE procedures.

### **6.3 REMOVAL OF PATIENTS FROM THERAPY OR ASSESSMENT**

Patients may be withdrawn from the trial prior to completion if any of the following criteria are observed:

1. Intercurrent illness or an adverse event, which requires discontinuation of treatment per protocol.
2. An acute COPD exacerbation (defined as an increase or new onset of more than one of the following respiratory symptoms [cough, sputum, sputum purulence, wheezing, dyspnea] with a duration of three or more days requiring treatment with antibiotics and / or systemic [oral, intramuscular or intravenous] steroids).
3. Required use of supplemental oxygen therapy.
4. Oxygen desaturation below 85% for at least 30 seconds during exercise testing.
5. Actively participating in a pulmonary rehabilitation program.
6. Request by the patient to withdraw from the study.
7. Administrative reasons (protocol violations, persistent non-compliance).
8. Decision by Boehringer Ingelheim to discontinue one or all patients.
9. During the treatment period, if the investigator judges that the patient requires initiation of chronic maintenance treatment with tiotropium.

No patient should be discontinued from the trial for a protocol violation before discussion with the clinical monitor.

### **Dropouts and Withdrawals**

To be considered complete, a patient must complete all study visits as specified in the protocol without violations of the protocol so significant as to obscure the response to treatment.

Patients who fail to complete all study visits and all of the testing as specified in the protocol will **not** be considered complete and may **not** be enrolled at a later date and will not be replaced. A record will be kept of all patients who fail to complete all study visits and their reasons for discontinuation.

Once a patient is randomized and treated, all observations outlined in the protocol should be performed, unless the patient withdraws consent at any time (without having to justify the decision). All available data from patients who discontinued during the trial, for whatever reason, will be included in the safety analysis. As noted in Sections 7.3 and 7.4, some data on incomplete patients will also be included in the efficacy analyses. Premature terminations will be reported to the sponsor.

## **7. STATISTICAL METHODS AND DETERMINATION OF SAMPLE SIZE**

### **7.1 STATISTICAL DESIGN / MODEL**

This is a 22-week, multi-centre, multi-national, randomized, double-blind, two-way cross-over study to evaluate the effects of the once-daily administration of tiotropium (Spiriva® HandiHaler®, 18 µg) and placebo on dynamic hyperinflation and physical exercise tolerance after six weeks of treatment in patients with early stage COPD. A mixed effect model for the IC change from baseline after six weeks of treatment, with terms of sequence, treatment, period as fixed effects, baseline as a covariate and subject within sequence as a random effect will be used for primary analysis. Detailed specifications will be provided in Section 7.3.

### **7.2 NULL AND ALTERNATIVE HYPOTHESES**

The treatment difference with tiotropium to placebo will be tested for isotime IC change from baseline at the level of  $\alpha = 0.05$  (two-sided). The primary hypothesis can be written as follows:

H0: Mean change from baseline of isotime IC after six weeks of treatment with tiotropium = Mean change from baseline of isotime IC after six weeks of treatment with placebo

H1: Mean change from baseline of isotime IC after six weeks of treatment with tiotropium ≠ Mean change from baseline of isotime IC after six weeks of treatment with placebo

Different baseline values will be used for the two treatment periods of the cross-over study.

Visit 3 will be the baseline for the first period, while Visit 5 (after wash-out) will be the baseline for the second period.

### **7.3 PLANNED ANALYSES**

The intent-to-treat (ITT) principle will be used to include as many patient periods as possible in the analysis. All randomized patients with at least one baseline data (at Visit 3 or Visit 5) and two non-missing post-dosing data (at Visit 4 and 6) for the primary endpoint will be included in the full analysis set (FAS). The primary analysis will be carried out on the FAS.

The subset of patients who complied with the protocol in essential criteria will be included in the per-protocol set (PPS). Patients included in the FAS who have important protocol violations will be excluded from PPS. A protocol violation will be considered important if it can be expected to have a distorting influence on the assessment of the primary endpoint. The final decision as to which patients are included in the FAS and PPS will be made prior to unblinding. Further details will be given in the trial statistical analysis plan (TSAP).

All patients treated with at least one dose of study drug (the treated set) will be included in the safety analyses.

A Trial Statistical Analysis Plan (TSAP) will be developed in which the details of the statistical analyses are specified.

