### **7.3.1 Primary analyses**

The primary analysis is a mixed effect model comparing the change from baseline of isotime IC after six weeks of treatment, with terms of sequence, treatment, period as fixed effects, baseline as a covariate, and subject within sequence as a random effect.

Adjusted mean values as well as treatment contrasts will be presented together with the 95% confidence intervals.

The primary analysis will be performed on the FAS.

A sensitivity analysis for the primary endpoint will be conducted for the PPS. This will only be done if the FAS and per-protocol set differ by more than 10% in size of the FAS population.

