### **7.3.2 Secondary analyses**

The mixed effect model as described for the primary endpoint will be performed for all continuous secondary endpoints. The adjusted mean values as well as the treatment contrasts will be presented together with the 95% confidence intervals.

For constant work rate exercise duration, log transformation will be applied before taking the difference from baseline.

For evaluation of perception of improvement on the exercise test, analysis will be exploratory only and will be summarized descriptively.

For categorical endpoint (the locus of symptom limitation), frequency tables by visit as well as a shift table of baseline versus six weeks after treatment will be provided.

All other data, including baseline demographics, baseline disease data, concomitant medication use, will be summarised descriptively using appropriate methods.

All secondary analyses will be performed on the FAS.

The other endpoints comparing COPD patients with Age / Gender Matched Controls will be summarized descriptively, with 95% confidence interval for continuous variable. The first 100 randomized patients and the Age / Gender Matched Controls will be included in the analyses.

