### **7.4 HANDLING OF MISSING DATA**

Every effort should be made to collect complete data on each test day. Missing value from Visit 4 and 6 will not be imputed. Missing value of baseline (Visit 3 or 5) will be imputed with the value from the other baseline if available. If not available the patient will not be included in the FAS.

Methods to handle any exceptional cases will be considered only before unblinding and will be documented.

With respect to safety evaluation, it is not planned to impute missing data.

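### The full analysis set requires isotime IC at both Visit 4 and Visit 6, so every efficacy analysis is a two-period completer analysis, against the protocol's own aim of using as many patient periods as possible

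*Protocol*

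**What the plan says.** Protocol Section 7.3 opens with the aim: "The intent-to-treat (ITT) principle will be used to include as many patient periods as possible in the analysis". The next sentence defines the full analysis set (FAS): randomised patients with at least one baseline "and two non-missing post-dosing data (at Visit 4 and 6) for the primary endpoint will be included in the full analysis set (FAS").

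The rule carries through the rest of Section 7:

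- Section 7.3.1: "The primary analysis will be performed on the FAS". The model has sequence, treatment and period as fixed effects, "baseline as a covariate, and subject within sequence as a random effect".
- Section 7.3.2: "All secondary analyses will be performed on the FAS".
- Section 7.4: "Missing value from Visit 4 and 6 will not be imputed". By contrast, "Missing value of baseline (Visit 3 or 5) will be imputed with the value from the other baseline if available".
- The only sensitivity analysis named for the primary endpoint uses the per-protocol set. Section 7.3 forms that set by removing patients from the FAS, and Section 7.3.1 runs the analysis only if the two sets differ by more than 10%.

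Section 7.6 assumes 20% drop-out and randomises 124 patients to obtain 100 in the analysis set.

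**The concern.** Under this rule every FAS patient contributes exactly two periods, so no single observed period can enter. A patient who completes Period 1 and then leaves is removed, with an observed baseline and an observed week-6 response. A patient whose baseline has to be borrowed from the other period is kept.

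Membership of the primary analysis set therefore depends on what happens after randomisation. The withdrawal reasons in Section 6.3 include exacerbation, desaturation during exercise and the investigator's judgement that the patient needs maintenance tiotropium. Appendix 10.3 withdraws patients whose exercise test is stopped for listed medical reasons. Such reasons could be related to a poor Period 1 response, and could be commoner after one treatment than the other. If so, those who remain are selected differently in the two sequences and the completer contrast is biased. The rule also makes missing isotime IC a reason for exclusion from the analyses of exercise duration, Borg scores, FEV1 and rescue use, even where those are observed.

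**Working it through.** **Inputs from the protocol (Sections 7.5 and 7.6).** Effect 100 ml; SD of change from baseline 340 ml; correlation r = 0.6 between period changes; two-sided alpha 0.05; power 90%; 1:1 allocation; 20% drop-out; 124 randomised, 100 analysed.

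**The plan's own figure.** SD of the within-patient difference = 340 × √(2 × (1 − 0.6)) = 304.1 ml. A paired t-test with the noncentral t gives N = 100, power 90.3%. All eight rows of Table 7.6: 1 reproduce. For drop-out, 100/0.8 = 125 against the stated 124, and 124 × 0.8 = 99.2. The sample size is not in error.

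**How many patients.** 124 − 100 = 24. This is an upper limit on discarded usable periods, because a patient who leaves before Visit 4 has no week-6 value under any rule.

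**Bias of the completer contrast.** With d = Period 1 minus Period 2 change, the estimate is (mean d in AB − mean d in BA)/2, where A is tiotropium. Suppose drop-out after Visit 4 depends on the Period 1 change and moves the mean Period 1 change of those retained by s. Their Period 2 mean moves by r × s, so d moves by (1 − r) × s. Hence

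bias = (1 − r) × (s_AB − s_BA)/2.

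If exactly the poorest fraction p of a sequence leaves, s = 340 × φ(z_p)/(1 − p).

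*One drop-out rule for both sequences, 20% overall, poorest leave.* The true 100 ml effect gives drop-out of 15.9% after tiotropium and 24.1% after placebo.
- s_AB = 340 × 0.2423/0.841 = 98.0 ml
- s_BA = 340 × 0.3116/0.759 = 139.6 ml
- bias = 0.4 × (98.0 − 139.6)/2 = −8.3 ml

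With a logistic rule instead, the bias is −2.2 ml at a log-odds slope of −1 per SD of Period 1 change and −4.8 ml at a slope of −2.

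*Unequal drop-out, 10% after tiotropium and 30% after placebo.*
- Poorest leave: s_AB = 340 × 0.1755/0.9 = 66.3 ml; s_BA = 340 × 0.3477/0.7 = 168.9 ml; bias = 0.4 × (66.3 − 168.9)/2 = −20.5 ml
- Logistic slope −1: s_AB = 30.9 ml; s_BA = 86.0 ml; bias = 0.4 × (30.9 − 86.0)/2 = −11.0 ml

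*Equal drop-out of 20% in each sequence by the same mechanism.* s_AB = s_BA, so the bias is 0.

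**Simulation.** 124 patients, r = 0.6, true effect 100 ml, 20% drop-out after Visit 4 under a common rule, no baseline covariate, 3000 runs per row (Monte Carlo error on power about 0.5 percentage points):

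| Drop-out depends on Period 1 change | FAS rule: mean, power | All available periods: mean, power |
|---|---|---|
| Not at all | 99.6 ml, 89.2% | 99.6 ml, 90.8% |
| Slope −1 | 97.6 ml, 89.1% | 99.9 ml, 90.7% |
| Slope −2 | 95.0 ml, 87.5% | 100.0 ml, 90.6% |
| Poorest leave | 91.5 ml, 87.7% | 99.6 ml, 91.7% |

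With no treatment effect and a common rule, the rejection rate under the FAS rule was 4.5% to 5.7%.

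**Precision alone.** Take 62 patients per sequence, 50 of them with both periods and the other 12 with Period 1 only. Per sequence, in units of 340², the variance of the Period 1 minus Period 2 contrast is:
- completers: 2(1 − 0.6)/50 = 0.0160
- all periods: (1 − 0.6)²/62 + (1 − 0.6²)/50 = 0.0026 + 0.0128 = 0.0154

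The ratio is 1.04, so the discarded periods are worth about 4 extra complete pairs per 100.

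**The case against.** The strongest reply is that little is at stake. The trial is sized on 100 patients in the analysis set and randomises 124 to get them, so power is already protected. At r = 0.6 the discarded periods add about 4 pair-equivalents, and only if all 24 drop-outs have Visit 4 data. The bias needs an assumed mechanism, and no withdrawal criterion in Section 6.3 refers to IC. Under a common rule with a true benefit the bias runs against tiotropium, and with no effect the type I error stayed near 5%. The all-period analysis looks unbiased in the simulation because drop-out was made to depend only on observed Period 1 data; informative drop-out beyond that was not tested. All of this stands. It limits the severity, but it does not reconcile the FAS rule with the sentence before it.

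Three stronger readings are tempting, and the protocol does not support them:

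- *That the Dropouts and Withdrawals text in Section 6.3 contradicts the FAS rule.* It says only that "some data on incomplete patients will also be included in the efficacy analyses". There, a patient is incomplete if any visit or test is missed. Patients lacking one baseline or only the Visit 7 call are incomplete in that sense and can still enter the FAS. The inconsistency lies within Section 7.3.
- *That one failed IC manoeuvre costs a patient all secondary data.* IC is measured at rest, every two minutes and at end of exercise (Section 5.1.1), and isotime values are interpolated for all but the shortest test (Section 2.2). One failure need not make the endpoint missing.
- *That the bias is larger because the correlation may be lower.* It does scale with (1 − r), but Section 7.6 commits to 0.6, and that value should carry the headline.

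**Conclusion.** The concern holds in a limited form. Section 7.3 states one principle and fixes a rule that defeats it. The rule governs the primary and all secondary analyses, and the named sensitivity analysis lies inside the same set, so it cannot reveal the consequence. This is not a detail left to the analysis plan, because the protocol itself fixes the rule.

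The size is modest: about −2 to −8 ml on 100 ml under a common drop-out rule, and about −11 to −20 ml under 10% versus 30% drop-out by first treatment. The sign reverses if tiotropium loses more patients, and the bias vanishes if selection is equal in both sequences. Under the common rules power is 87.5% to 89.2%, against 90.6% to 91.7% with all periods. These figures assume r = 0.6, SD 340 ml, all drop-out after Visit 4, and dependence on the observed Period 1 change. The protocol supports the first two; the timing and mechanism are assumptions. It should be fixed, but it does not invalidate the design or the sample size.

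**What to change.** 1. In Section 7.3, define the FAS as randomised, treated patients with at least one post-dose value (Visit 4 or Visit 6) and a baseline (own-period, or imputed under Section 7.4) for the endpoint analysed. Apply this endpoint by endpoint.
2. In Sections 7.3.1 and 7.3.2, fit the stated mixed model to all available periods.
3. In Section 2.2, state that isotime is the minimum over the Visit 3 to Visit 6 tests actually performed.
4. Keep the two-period completers as a sensitivity analysis, and align Section 7.4 and the analysis plan.

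The cost is a short wording change before unblinding, with no new data. There are two downsides. Isotime for a one-period patient is a minimum over fewer tests, so the change touches the primary endpoint definition as well as the analysis set. And the all-period analysis is unbiased only if drop-out depends on observed data, which is a further reason to report the completer analysis beside it.
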